## Abstract

**Background:**

Unplanned hospital presentations may occur post-stroke due to inadequate preparation for transitioning from hospital to home. The *Re*covery-focused *C*ommunity support to *A*void readmissions and improve *P*articipation after *S*troke (ReCAPS) trial was designed to test the effectiveness of receiving a 12-week, self-management intervention, comprising personalised goal setting with a clinician and aligned educational/motivational electronic messages. Primary outcome is as follows: self-reported unplanned hospital presentations (emergency department/admission) within 90-day post-randomisation. We present the statistical analysis plan for this trial.

**Methods/design:**

Participants are randomised 1:1 in variable block sizes, with stratification balancing by age and level of baseline disability. The sample size was 890 participants, calculated to detect a 10% absolute reduction in the proportion of participants reporting unplanned hospital presentations/admissions, with 80% power and 5% significance level (two sided). Recruitment will end in December 2023 when funding is expended, and the sample size achieved will be used. Logistic regression, adjusted for the stratification variables, will be used to determine the effectiveness of the intervention on the primary outcome. Secondary outcomes will be evaluated using appropriate regression models. The primary outcome analysis will be based on intention to treat. A *p*-value ≤ 0.05 will indicate statistical significance. An independent Data Safety and Monitoring Committee has routinely reviewed the progress and safety of the trial.

**Conclusions:**

This statistical analysis plan ensures transparency in reporting the trial outcomes. ReCAPS trial will provide novel evidence on the effectiveness of a digital health support package post-stroke.

**Trial registration:**

ClinicalTrials.gov ACTRN12618001468213. Registered on August 31, 2018.

SAP version

1.13 (October 12 2023)

Protocol version

1.12 (October 12, 2022)

SAP revisions

Nil

**Supplementary Information:**

The online version contains supplementary material available at 10.1186/s13063-023-07864-2.

## Introduction

About one in three people discharged from hospital after an acute stroke experience an emergency department presentation or an unplanned readmission within 90 days of discharge [1]. Unplanned hospital readmissions are often related to suboptimal preparation and support of survivors or their carers in transition from hospital to home [1, 2], including lack of ongoing self-management support to assist with ongoing disability or complications after stroke [3]. Therefore, there is an urgent and unmet need for innovative, accessible self-management support and education programmes that align with the recovery and lifestyle goals of people living with stroke [4].

In the *Re*covery-focused *C*ommunity support to *A*void readmissions and improve *P*articipation after *S*troke (ReCAPS) trial, adults with stroke are randomised to either receive a 12-week digital health self-management support package within 2 weeks of discharge from hospital to home or control [5]. The intervention comprises personalised goal setting with a clinician within 14 days of returning home and assignment of educational or motivational messages to support self-management and goal attainment that allow for progression in skill development. The messages are delivered via a short message service (SMS) or email depending on the preferred contact method of the participant. The control group receives up to seven administrative text messages (e.g. a link to the Stroke Foundation website), but no healthcare messages. The primary hypothesis is that, compared to control participants, there will be a 10% reduction in the proportion of intervention participants who had unplanned hospital presentation (emergency department/admission) within 90 days after randomisation. The main secondary outcomes include goal attainment, self-efficacy, self-management, education attainment, unmet needs, resources used, mood, and quality of life, at 90-day post-randomisation. We present the statistical analysis plan for the ReCAPS trial.

## Methods

This statistical analysis plan has been written according to the “Guidelines for the Content of Statistical Analysis Plans in Clinical Trials” [6]. The study protocol has been described in detail previously [5] and is briefly outlined in the sections below. In addition, details of the initial study design, and any subsequent changes made, have been published on the Australian and New Zealand Clinical Trials Registry (number: ACTRN12618001468213). This statistical analysis plan comprises details of approaches to be used for the analysis of primary and secondary outcomes.

### Trial design

This is a prospective, multicentre, randomised controlled trial, with 1:1 allocation ratio, blinded assessment of outcomes, and intention-to-treat analysis.

### Randomisation and blinding

Randomisation is undertaken through the REDCap online system [7], with stratification balancing by age (< 65 or 65+ years) and level of disability (based on a baseline modified Rankin Scale [scores 0–2 for none-minor disability, 3–4 for moderate-severe disability]). The randomisation table, comprising the allocation sequence, block sizes, and stratification balancing, was developed outside of REDCap by an independent data analyst and imported into the REDCap study database.

The trial has a double-blind design. Therefore, hospital staff, participants, outcome assessors, and trial biostatisticians are unaware of group allocation. To ensure that blinding of participants to group allocation is maintained, the trial is described in the patient information and consent form in general terms as “providing post-hospital discharge support” [8]. Specifically, intervention approaches were broadly described in the patient information and consent form as including the “setting of specific recovery goals with trained clinicians, receiving electronic self-management information sent via SMS or email, and participation in follow-up assessments”. Outcome assessors also use an interview script to standardise outcome assessments undertaken by telephone interview and are trained to avoid entering into general discussions. To ensure hospital clinicians and participants are unaware of the allocation group, all eligible consenting patients complete goal setting, using the ReCAPS “goal setting menu”, and data collection at baseline is standardised. The trial biostatistician who will undertake the analysis is also blinded to group allocation.

### Sample size calculation

At the time we designed the trial, we were required to use indirect evidence to estimate the potential effect size of our novel intervention for the primary outcome. We estimated a sample size of 890 participants (445 participants in each intervention group) to allow sufficient power for the primary outcome analysis. The power calculation was based on the following: (a) a conservative estimate (33%) of participants in the control group having unplanned hospital presentations (emergency department/admission) within 90 days, based on data from the *Australian Stroke Clinical Registry* (*AuSCR*) linked to hospital emergency department presentations and admissions data in four states [1] and adjusted for the study inclusion criteria (being aged ≥ 18 years and discharged to home), (b) a 10% absolute reduction in unplanned hospital presentation (emergency department presentations or readmissions) within 90 days of randomisation in the intervention group vs. controls [9], (c) a ≥ 80% power at the significance threshold of *α* = 0.05 two-tailed and (d) an assumed attrition rate of 20% due to drop-out, refusal or loss to follow-up. Using an adaptive sample-size procedure we had pre-planned to re-estimate the sample size once, two-thirds of the original sample size outcomes had been obtained. Issues with recruitment during the COVID-19 pandemic and the current recruitment rate and available budget mean that this sample size is now infeasible to achieve.

The trial will be closed to recruitment by the end of December 2023, when our funding is expended with whatever number of participants is obtained by that time. This number will be used without any re-estimation of power. Using the observed data on retention rate (currently 93%), and more recent data on unplanned hospital presentations/readmissions from another study [10], our sample may provide sufficient power for a 10% difference in the primary outcome.

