## Statistical principles

### Confidence intervals and p-values

Statistically significant results will be identified using two-sided 5% significance levels. Estimates of this trial will be reported with 95% confidence intervals.

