## Current status of the trial

As of 20th of December 2023, 462 participants have been recruited and randomised. Recruitment to the trial was affected significantly by the COVID-19 pandemic and thereafter. Due to funding constraints, recruitment will conclude in December 2023. Data lock is anticipated for the second quarter of 2024, when all 90-day follow-up assessments should have been completed. Further details on analyses of longer-term outcomes to be determined through data linkage, including resource utilisation/costs within 12 months and composite (cardiovascular or death) outcomes, will be reported separately.

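### The statement that the reduced sample may have sufficient power for a 10-point difference is unsupported at any control rate the document gives; at 33% the power is about 64%

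*SAP article*

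**What the plan says.** Under Sample size calculation, the SAP article bases the design on "a conservative estimate (33%) of participants in the control group having unplanned hospital presentations" within 90 days and on "a 10% absolute reduction in unplanned hospital presentation". It asks for at least "80% power at the significance threshold of" 0.05, two-tailed, and allows 20% attrition. The result is 890 participants, 445 per arm. The same section calls this number infeasible. Recruitment closes at the end of December 2023 with whatever has been reached, and of that number it says: "This number will be used without any re-estimation of power".

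The next sentence nevertheless draws a conclusion about power. From the observed retention (93%) and more recent event data in another study, it says that "our sample may provide sufficient power for a 10% difference in the primary outcome". It prints neither the newer event rate, nor the number expected in the analysis, nor a power figure.

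The size of the sample appears later, under Current status of the trial: "As of 20th of December 2023, 462 participants have been recruited and randomised". The Methods/design part of the abstract gives 890 "with 80% power and 5% significance level (two sided") and adds that the number achieved will be used. It does not say how far short that number falls.

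**The concern.** The sample is about half the target (462/890 = 52%). Better retention than planned (93% against 80%) makes up only part of that: the analysable number falls from 890 × 0.80 = 712 to 462 × 0.93 = about 430. A statement that power may still suffice for the same absolute difference therefore depends on the event rate, and that is the input the section leaves out. The only control rates in the document are the 33% in the design and the figure of about one in three in the Introduction.

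The 10-point reduction is the trial's primary hypothesis. If the result is not statistically significant, a reader will turn to this section to judge whether the trial could have detected that effect, and the section gives nothing that can be checked.

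**Working it through.** **Inputs.** Control rate 33%, absolute reduction 10 points (so 23% with the intervention), power at least 80%, attrition 20%, target 890: Sample size calculation. Two-sided 5%: Confidence intervals and p-values. Allocation 1:1: Trial design. 462 randomised: Current status of the trial. Retention 93%: Sample size calculation.

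**Method.** Two-proportion normal approximation with pooled variance under the null, n analysed per arm, d = p1 − p2, p̄ = (p1 + p2)/2:

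power = Φ( [d − 1.96·√(2p̄(1−p̄)/n)] / √([p1(1−p1) + p2(1−p2)]/n) )

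**Step 1, the plan's own figure.** For 33% against 23% at exactly 80% power, n = [1.96·√(2×0.28×0.72) + 0.8416·√(0.33×0.67 + 0.23×0.77)]² / 0.10² = 315.3, so 316 per arm, or 632. With 20% attrition, 632/0.80 = 790. A continuity correction gives 335 per arm, or 838. Neither equals 890, but 890 meets the stated target of at least 80%: 445 × 0.80 = 356 per arm gives 84.6% power (82.5% with continuity correction). The original target is not in question.

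**Step 2, the achieved sample at 33%.** 462 × 0.93 = 429.7, or 214.8 per arm.

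- Null term: 1.96 × √(2×0.28×0.72/214.8) = 0.0849
- Standard error under the alternative: √(0.3982/214.8) = 0.0431
- Power: Φ((0.1000 − 0.0849)/0.0431) = Φ(0.35) = 63.7%

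Other methods give 64.2% (unpooled), 63.9% (arcsine) and 59.6% (continuity-corrected). With no attrition at all (231 per arm) power is 66.9%. Reaching 80% at 93% retention needs 316/0.93, rounded up to 340 per arm, or about 680 randomised. A few late recruits in December would not change the picture.

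**Step 3, detectable difference.** At a 33% control rate with 214.8 per arm, power is 76.5% for 11.5 points and 80.2% for 12 points.

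**Step 4, the missing input.** Because the newer rate is not printed, the 10-point drop is run over a range of assumed control rates:

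| Control rate | Intervention rate | Power, 214.8 per arm |
|---|---|---|
| 20% | 10% | 82.9% |
| 21% | 11% | 80.9% |
| 21.5% | 11.5% | about 80% |
| 22% | 12% | 79.0% |
| 25% | 15% | 73.8% |
| 30% | 20% | 66.9% |
| 33% | 23% | 63.7% |
| 40% | 30% | 58.5% |
| 50% | 40% | 54.9% |

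A higher rate than planned makes things worse until the rate becomes implausibly high (82.9% power returns at a 90% control rate). The useful crossing point is therefore about 21.5%, where the drop is 10/21.5 = 47% of the control rate, against 10/33 = 30% at the design rate. With a continuity correction the crossing point lies just below 20% (79.3% power at 20%, 81.5% at 19%).

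**The case against.** The strongest objection is that 64% does not test the sentence. The section does not claim sufficiency at 33%. It cites newer event data in place of that rate, and the source cannot be seen here. If that source gives about 21.5% or less, the sentence is right. It is also hedged. This stands, and it limits the point: a reader might infer that the plan makes a false claim or an arithmetic error, but no power figure is printed for the reduced sample and the rate behind the sentence is unknown.

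Three further inferences are tempting and should not be drawn.

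- **That the trial misses a true 10-point effect more than one time in three.** This holds at 33% (miss rate 36%) but not at 25% (26%). It needs its condition.
- **That the design assumed a 30% relative reduction and must be judged on it.** The plan states an absolute target. The relative figures above are conversions, useful only to show what 10 points would mean at a lower rate.
- **That the abstract claims 80% power for the sample obtained.** It gives 890 as the calculated size and says the achieved number will be used; the body says 890 is infeasible. A clearer label would help, but the shortfall is not concealed.

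Nor does the plan say that a non-significant result will count as evidence of no effect; it commits to 95% confidence intervals.

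The objection does not supply the missing rate. A statement about the power of the primary analysis should be checkable, all the more when the sentence before it says that power will not be re-estimated.

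**Conclusion.** The concern holds as a point about an unsupported statement. With 462 randomised and 93% retained, power for a 10-point absolute drop is about 64% at the plan's own 33% control rate, and the difference detectable with 80% power is about 12 points. At no control rate printed in the document does the sample reach 80%. It does so only at about 21.5% or lower, and the document does not say whether the newer study's rate is that low.

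The figures rest on equal arms, a final number close to 462, retention staying at 93%, two-sided 5%, and a simple comparison of two proportions. They ignore clustering by hospital and adjustment for the stratification variables, for which the document gives no figures.

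**What to change.** In Sample size calculation, replace the sufficiency sentence with:

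- the number expected in the analysis (about 430, or the final count);
- the control rate taken from the newer study;
- the power for a 10-point absolute drop at that rate and at 33% (about 64%), with a short table over control rates of 20% to 33%.

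If the newer rate cannot be stated, drop the claim of sufficiency. In the abstract and in this section, label 890 and 80% power as the original target that was not reached.

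The cost is wording only. The stated power becomes less favourable; no extra patients are needed, and the primary model and outcome definitions are untouched.

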### Framework

All outcome analyses will be conducted to determine the effectiveness of the ReCAPS intervention over the control intervention (described in detail below).

### Statistical interim analyses and stopping guidance

An independent Data Safety and Monitoring Committee (DSMC) was established to safeguard the interests of trial participants, by assessing the safety of the intervention during the trial, and the general progress of the trial. The committee comprises one neurologist, a senior academic physiotherapist who has expertise in digital health randomised clinical trials and a senior clinical trials biostatistician. Specifically, the role of the DSMC is as follows: (a) periodically monitor and review participant safety in the trial, (b) monitor effectiveness, and (c) review participant recruitment, accrual, retention, and withdrawal.

The DSMC met at least once per year until November 2020 and have met twice per year subsequently, with a total of seven meetings as of September 2023. The committee recommended the trial to continue based on the interim analysis of the primary outcome from the first 50 participants (~6% of the estimated sample size). All interim analyses are being undertaken by a data analyst who is blinded to the group allocation. The principal investigator has the responsibility to report data on any severe adverse events to the DSMC and the independent medical monitor, if needed. The medical monitor is a neurologist who reviews serious adverse events, if deemed to be related to the intervention, and adjudicates on unplanned/planned hospital readmissions. The DSMC is also tasked with formulating recommendations relating to the selection/recruitment/retention of participants, participant management, improving adherence to protocol-specified regimens, and the procedures for data management and quality control based on these interim analyses.

There are no strict stopping criteria, but the DSMC have a responsibility to provide recommendations about continuing, modifying, or stopping the trial, in line with the DSMC charter. Following an interim analysis, the trial may be stopped for safety reasons without rejecting any null hypotheses, i.e. there is no planned adjustment of the significance level due to interim analyses. 

### Timing of outcome assessments and final analysis

The primary outcome assessment is undertaken at 90 days (~13–15 weeks) after randomisation. The schedule of assessments for secondary outcomes ranges from baseline to 90 days post-randomisation and 12 months post-randomisation (Table 1). All outcome analyses will commence after all assessments and evaluations are completed.

**Table 1 Tab1:** List of study outcome

Assessment	Baseline	Follow-up^a^	
		90 days	12 months
Primary outcome			
Unplanned hospital presentation^b^		✓	
Secondary outcomes			
Goal attainment post-stroke^c^		✓	
Stroke self-efficacy^c^	✓	✓	
Anxiety and depression^c^	✓	✓	
Number of hospital contacts^d^		✓	✓
Health-related quality of life^c^	✓	✓	✓
Cost-effectiveness^c,d^	✓	✓	✓
Composite outcome^d,e^		✓	✓
Health education assessment post-stroke^c^	✓	✓	
Self-management post-stroke^c^	✓	✓	
Healthcare resource utilisation^c,d^	✓	✓	✓
Modified Rankin Scale^c^	✓	✓	
Long-term unmet needs^c^	✓	✓	

^a^Undertaken by blinded ReCAPS researchers at 90 days and 12 months post-randomisation. ^b^Includes emergency department presentations and unplanned hospital admission. ^c^Option for self-assessment by participants. ^d^Obtained through self-report and linkage with administrative data. ^e^Includes recurrent stroke, cardiovascular events, or deaths

## Statistical principles

### Confidence intervals and p-values

Statistically significant results will be identified using two-sided 5% significance levels. Estimates of this trial will be reported with 95% confidence intervals.

### Adherence and protocol deviations

Intervention fidelity will be assessed throughout the trial at both the research-team and practitioner-patient level and will be monitored throughout the trial by an external research team. This will include monitoring goal setting procedures, telephone interviews, the dispatch logs from the electronic messaging gateway, and follow-up assessments. The intervention fidelity procedures have been developed to address five key areas of the study: (a) study design, (b) training documents and processes, (c) delivery of the ReCAPS intervention, (d) receipt of intervention as per protocol, and (e) adaptations that occur to any protocol processes throughout the study (Supplemental Table I). This approach is consistent with the Behaviour Change Consortium treatment fidelity recommendations [11].

Any participant treated in a manner that deviates from the protocol may be excluded from per-protocol analyses. The nature and reasons for any protocol deviation are recorded in the electronic case report form (eCRF).

### Analysis populations

Analysis of the primary outcome will be based on the principle of intention to treat and will comprise all randomised patients. Further per-protocol analyses will be undertaken among participants who complete at least 10 of 12 weeks of the intervention to which they were randomised, irrespective of the number of goals achieved or messages received.

## Trial population

### Screening, eligibility, and recruitment

To determine the representativeness of the trial cohort, we will compare characteristics of patients who were screened with those who participated. At the end of the trial, we will obtain a list of AuSCR registrants from participating hospitals that met the eligibility criteria to compare characteristics of those included in the trial with those eligible but who did not participate. Details of recruitment and eligibility criteria are described in the trial protocol [5], and information on eligibility, recruitment, and withdrawal/follow-up will be reported in a CONSORT flow diagram (Fig. 1). Variables to be requested will include demographic (e.g. sex, age) and clinical data (type of stroke, time since stroke, history of previous stroke). These data will be provided to the Monash staff using the project ID number allocated by AuSCR data custodians, excluding personal identifying variables.

**Fig. 1 Fig1:**
[figure not shown]
CONSORT flow diagram

### Baseline patient characteristics

Data on baseline characteristics will be summarised as frequencies and proportions for categorical variables and medians and interquartile ranges for continuous variables (Supplemental Table II).

## Analysis

### Outcome definitions

#### Primary outcome

The primary outcome is the proportion of participants who report having an “unplanned” hospital presentation (emergency department/admission) within 90 days following randomisation. This will be determined via self-report and confirmed through linkage with hospital data, as described below.

